CPAP devices (intervention arm) and high-concentration oxygen therapy masks (control arm) will be packaged in identical equipment boxes measuring approximately 170 mm × 170 mm × 70 mm. The boxes will be tamper-proof and equal in weight and appearance to maintain allocation concealment. Boxes can only be opened after a patient is definitively enrolled in the trial. Once a box is opened when attending a patient, that patient will be included in the study as per allocated treatment. It will not be possible to re-seal the box. Equipment boxes will be assembled, numbered and sealed in accordance with the allocation sequence by researchers not directly involved in the conduct of the trial, under the supervision of the trial manager. Boxes will then be transferred to the central WMAS storage and distribution centre where they will be held in an access-restricted research store. Boxes will subsequently be supplied to participating ambulance hubs as required by the WMAS internal distribution team and held locally in a designated storage area. Ambulance service clinicians will then collect an equipment box at the beginning of each shift. At the end of the shift, boxes will be returned to the ambulance hub equipment store. Boxes will be signed in and out for each shift with ambulance service clinician, ambulance and equipment box details recorded in a distribution log. Research paramedics will monitor the condition, status and location of boxes on a weekly basis to ensure concealment of the allocation sequence until treatment assignment occurs.

Ambulance service clinicians (paramedics, ambulance technicians, paramedic practitioners or critical care paramedics) will identify patients with ARF when attending 999 ambulance calls. Patients meeting trial inclusion criteria will be approached for enrolment in the trial guided by a standardised script. If possible, verbal consent will be obtained for participation prior to enrolment. Patients lacking capacity will be enrolled according to a hierarchical consent process complying with the Mental Capacity Act (MCA) 2005 [14] described below. Immediately after inclusion, ambulance service clinicians will open the trial equipment box and provide treatment according to whether a CPAP device or high-concentration oxygen mask is supplied.

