### Consent

A hierarchical consent process will be used complying with the Mental Capacity Act (MCA) 2005 [14]. Verbal consent will be obtained for enrolment if the treating ambulance service clinician determines that the patient has capacity. Ambulance service clinicians will enrol patients without consent if the patient does not have capacity. In either case, a research paramedic will review the participant in hospital as soon as possible after enrolment, provide verbal and written information regarding the study and seek written informed consent as soon as the participant has capacity. If the patient does not regain capacity, we will seek advice from a personal consultee for enrolment in the trial [15]. When a personal consultee is unavailable, a nominated consultee will be approached for a consent waiver [15]. If patients (or their consultees) decline consent, all non-identifiable data up to the point of refusal will be retained. No further data collection will be conducted from this point onwards, except for anonymised 30-day mortality data.

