#### Intervention arm

CPAP is a form of non-invasive ventilation (NIV) where oxygen or air is supplied to the upper airways at increased pressure [16]. The ACUTE trial will use the O_two unit, a lightweight, open, single-use, low-flow CPAP system [17]. The device consists of tubing, which is connected to an oxygen source (either a portable oxygen cylinder or the usual ambulance oxygen flow regulator), and an in-line CPAP unit connecting to a close-fitting face mask. The CPAP unit entrains ambient air to increase local mask pressure, providing resistance for the patient to breathe against. The level of CPAP is varied by altering the incoming oxygen flow rate. Thus, the inspired concentration of oxygen varies according to the desired degree of CPAP, as the flow rate is altered. As an open system, with access to ambient air, the device allows unrestricted inspiratory flows and is unaffected by respiratory rate.

Treatment may be commenced at the site of initial clinical contact or after transfer to an ambulance. An appropriately sized mask will be used, with CPAP started at 5 cm H_2_O and then incrementally increased by 1 cm H_2_O every 2–5 min to a maximum of 15 cm H_2_O according to BTS peripheral oxygen saturation targets [13] measured by standard pulse oximetry. Target peripheral oxygen saturations will be 88–92% for patients with known/suspected COPD and 94–98% for patients with other suspected causes of acute respiratory failure. If necessary, nebuliser treatments can be positioned between the face mask and the O_two CPAP unit. CPAP will be continued until arrival at hospital unless not tolerated (e.g. patient request, claustrophobia, anxiety, significant agitation); patient is unable to maintain own airway; decrease in systolic blood pressure to < 90 mmHg; vomiting; epistaxis; conscious level decreases and patient does not respond to voice; patient improvement; or suspected pneumothorax.

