### Data collection

A recruitment form (case report form (CRF) A), contained within each equipment box, will be completed every time a patient is enrolled in the trial. This will record study number, basic demographic details, eligibility criteria, suspected prehospital diagnosis,, consent details and limited clinical and treatment data not routinely recorded, including a patient and ambulance service clinician completed VAS dyspnoea scale (1–10) recorded on initial assessment and immediately before ED arrival. Routinely collected baseline characteristics, EMS timings, details of treatments provided and vital signs (including peripheral oxygen saturations) en route to hospital will be extracted from the ambulance service patient report forms/electronic patient records into ACUTE case report form B (CRF B) by research paramedics. At 30 days, research paramedics will also review the hospital records to record details of subsequent progress, treatments provided (including time to receiving hospital NIV, if provided), length of hospital stay, use of critical care, any adverse events (AEs) and status at 30 days. Any related AEs or serious AEs will be recorded on the study case report form (CRF B).

Baseline quality of life assessments will be performed by research paramedics shortly after hospital admission, following confirmation of patient consent for participation in the trial. Patients, or their representatives, will be asked to estimate their current health status, using the EQ-5D-5L. This data will be recorded in the study case report form (CRF B). Quality of life and resource use will also be assessed remotely by questionnaire at 30 days following enrolment. Participants will be asked for their preferred method for data collection, either telephone or postal. Initial non-responders will be contacted again after a further 2 weeks by telephone or post. Key elements of health care resource use to be recorded will include hospital services and GP or community services. Participants will also be asked to report any AEs in the 30-day follow-up questionnaire. For patients’ declining consent for follow-up, anonymised 30-day mortality will be recorded. The assessments and follow-up for the ACUTE trial are summarised in Table 2.

**Table 2 Tab2:** Summary of data collection and trial documentation

What	Where	Who	How		When	
				Baseline	Hospital admission	30 days
Consent form						
•Verbal consent	Scene of incident	Paramedics	Verbal	X		

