•Written informed consent	Hospital	Research paramedic	Paper		X	
Case report form A						
•Patient demographics	Scene of incident/emergency department	Paramedics	Paper	X		
•Patient characteristics			Telephone	X		
•Prehospital treatments •Adverse events				X X		
Case report form B						
•Patient demographics	Hospital	Research paramedic	Paper		X	
•Baseline quality of life					X	
•Inpatient treatments						X
•30-day mortality						X
•Intubation						X
•Critical care admission						X
•Length of stay •Adverse events					X	X
Patient questionnaire						
•Quality of life	Home	Patient	Paper			X
•Resource use		Research paramedic	Telephone			X
•Adverse events						X
Paramedic questionnaire						
•Acceptability of CPAP	Home/work	Paramedics	Electronic	X		
HRA safety report form						
•Unexpected related serious adverse events	CTRU	Chief investigator	Electronic	X	X	X
SAE form						
•Other serious adverse events	CTRU	Chief investigator	Paper	X	X	X

*CTRU* clinical trials and research unit, *SAE* serious adverse event, *CPAP* continuous positive airways pressure

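### The EQ-5D-5L labelled baseline is taken in hospital after allocated treatment, so the mean-change objective subtracts any effect already present, and it conflicts with the EQ-5D-5L outcome given elsewhere

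*Protocol article*

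**What the plan says.** On timing, the Data collection section states: "Baseline quality of life assessments will be performed by research paramedics shortly after hospital admission, following confirmation of patient consent". On content, it continues: "Patients, or their representatives, will be asked to estimate their current health status, using the EQ-5D-5L". Table 2 has separate columns for baseline and hospital admission, and it marks the row "Baseline quality of life" under hospital admission.

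Allocated treatment comes earlier. The section on randomisation and enrolment says: "Immediately after inclusion, ambulance service clinicians will open the trial equipment box and provide treatment". The Intervention arm section says: "CPAP will be continued until arrival at hospital unless not tolerated". Written consent follows in hospital, where research paramedics "seek written informed consent as soon as the participant has capacity", with a consultee route if capacity does not return. After a refusal, "No further data collection will be conducted from this point onwards, except for anonymised 30-day mortality data".

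The secondary objectives (Study design, aims and objectives) include the mean change in quality of life on the EQ-5D-5L, for the whole trial and per treatment group. The effectiveness list under Sample size and statistical analyses gives the mean EQ-5D-5L, with no mention of change. The Abstract lists EQ-5D-5L together with resource use at 30 days.

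**The concern.** A change score compares arms fairly when its starting value is taken before allocation, because randomisation then makes that value equal in expectation. Here the starting value can already carry a treatment effect. An arm that improved early would start higher and show less gain, even if its patients were better off at 30 days. This is a live possibility in this trial: the Background gives as a rationale that CPAP may work better when started on the way to hospital.

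Availability is a second issue. The value exists only for patients who reach the assessment and whose consent is confirmed. Some values come from representatives, whereas Table 2 presents the 30-day form as a patient questionnaire.

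What is at stake is modest but real. The objectives section says the clinical summaries will inform the design of a definitive trial, so a mislabelled baseline could be carried forward into it.

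**Working it through.** **1. Order of events in the article**

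- Allocation at 5–10 minutes and treatment at 10–60 minutes (Table 1).
- CPAP until hospital arrival, unless a listed stopping reason occurs (Intervention arm).
- Consent in hospital; Table 1 marks informed consent again at 1–29 days.
- First EQ-5D-5L after admission and after that consent (Data collection; Table 2).
- Second EQ-5D-5L by questionnaire at 30 days.

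The article describes no EQ-5D-5L before allocation and no recall of health before treatment. The in-hospital value is thus the only one from which a change to 30 days could be formed. The dyspnoea VAS is handled differently: its first score is taken on initial assessment.

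**2. What the change score estimates**

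The plan states no EQ-5D figure, so there is none to reproduce. The projected definitive sample size of 1518 rests on 30-day survival and is not affected.

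Let τ0 be the CPAP-minus-oxygen difference in mean EQ-5D-5L at the in-hospital assessment, and τ30 the difference at 30 days, among patients with both values.

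Difference between arms in mean change = τ30 − τ0.

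With a true pre-allocation baseline, τ0 would be 0 in expectation. With the in-hospital value, write f = τ0 / τ30. The contrast becomes τ30 × (1 − f), so f is the share removed. The article supplies neither τ0 nor τ30. Two assumed values of τ30 give:

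| f | Contrast if τ30 = 0.08 | Contrast if τ30 = 0.04 |
|---|---|---|
| 0 | 0.08 | 0.04 |
| 0.25 | 0.06 | 0.03 |
| 0.5 | 0.04 | 0.02 |
| 0.75 | 0.02 | 0.01 |
| 1 | 0 | 0 |
| 1.25 | −0.02 | −0.01 |

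Example: 0.08 × (1 − 0.5) = 0.04. The difference in 30-day means, without subtraction, stays at 0.08 (or 0.04) in every row.

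**3. The EQ-5D-5L outcome, place by place**

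| Place | EQ-5D-5L outcome |
|---|---|
| Abstract, Methods | listed with resource use at 30 days |
| Secondary objectives | mean change |
| Table 1 | quality of life only in the 30–37 day column |
| Data collection; Table 2 | in-hospital value called baseline, plus 30 days |
| Sample size and statistical analyses | mean |

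The change score appears in one place only, and the in-hospital assessment is absent from Table 1.

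**The case against.** The strongest reply is that the change score is hardly planned at all. It stands once, in the objectives, while the Abstract, Table 1 and the analysis section point to EQ-5D-5L at 30 days or its mean. Reporting is descriptive, with confidence intervals, and no between-arm test of EQ-5D-5L is stated. The outcome is secondary in a pilot of 120 patients. This stands, and it limits the severity. It does not remove the contradiction, and per-arm mean changes printed side by side invite the very comparison worked through above.

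A second reply is that an in-hospital assessment after consent is what an emergency trial can manage. That also stands: the objection is to the label and the subtraction, not to collecting the value. The restriction to consented or represented patients follows from the consent process, and no rewording removes it.

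Three stronger readings are tempting, and the article does not support them.

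- *Deaths drop out of EQ-5D-5L and count as short hospital stays.* The article gives no rule for deaths in either outcome. That is commonly left to the full protocol or the SAP, neither of which is shown. The direction for length of stay would also depend on when deaths occur.
- *The change score necessarily removes part of the CPAP effect.* The share depends on the early effect, which is unknown and may be nil.
- *The economic model is biased.* The Health economics section takes effectiveness from short-term mortality through odds ratios, and nothing there says that an EQ-5D-5L change score enters the model.

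**Conclusion.** The point holds as a low-severity error of labelling and outcome definition. The EQ-5D-5L called baseline is a post-randomisation, post-treatment value available only after consent, and this follows directly from the text without assumptions. Subtracting it turns the between-arm comparison into τ30 − τ0. How much this matters cannot be settled from the article: the table in the working rests on assumed 30-day effects of 0.04 and 0.08 and an assumed range for f, and serves only as illustration. The disagreement between the secondary objective and the Abstract and analysis section is a plain contradiction and needs resolving in any case. Feasibility outcomes, 30-day survival and the projected definitive sample size are unaffected.

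**What to change.** - In the secondary objectives, replace mean change with EQ-5D-5L at 30 days, for the whole trial population and by arm. State the 30-day time point in the effectiveness list under Sample size and statistical analyses, to match the Abstract.
- In Data collection and Table 2, rename the in-hospital value as an early post-treatment EQ-5D-5L. Show that assessment in Table 1 too.
- State that the early value will be reported descriptively by arm, and will be neither subtracted from the 30-day value nor used for adjustment as if it were a pre-treatment baseline.

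The cost is a wording change. Both assessments are already planned, so no data collection changes, even though recruitment has begun. The article would no longer offer a quality-of-life change from baseline, but nothing is lost by that, since no pre-treatment value is described. Any gain in precision from adjusting for the early value is also given up, which is acceptable for a descriptive summary.

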### Data management

All data will be collected and retained in accordance with the UK Data Protection Act 1998 and University of Sheffield clinical trials and research unit (CTRU) standard operating procedures (SOPs). Trial data will be extracted from source documents and CRFs and entered onto a secure data management system. Patient identifiable data (names, date of birth and contact details) will only be collected and entered on the prospect database when written informed consent has been confirmed. Validation reports will be run regularly to check the study data for completeness, accuracy and consistency. Discrepancies will be generated, monitored and managed by research paramedics to resolution.

### Sample size and statistical analyses

Participant recruitment and retention will be presented with a CONSORT flow diagram [18]. The following feasibility outcomes will then be reported descriptively for the whole trial population, together with their 95% confidence interval (calculated using the Wilson score method) [19]:Recruitment rate per 100,000 population per year (target 8, i.e. 120 across the 1.5 million population of the 4 WMAS hubs)Proportion recruited in error and classified as minor or major non-compliances (target 0 and ≤ %)Adherence to the allocation schedule (target ≥ 90%)Adherence to treatment in the CPAP arm (target ≥ 75%)Retention at 30 days (target ≥ 90%)Data completeness (target ≥ 90%)

Summary estimates of effectiveness outcomes will also be reported, for the whole trial population and separately per treatment group, with 95% confidence intervals using an as-randomised analysis:Proportion surviving to 30 daysProportion undergoing endotracheal intubation by 30 daysProportion admitted to critical care at any point up to 30 daysMean and median length of hospital stayChange in VAS dyspnoea score from initial presentation versus immediately before ED arrivalMean EQ-5D-5LKey elements of health care resource use up to 30 days

The ACUTE feasibility study aims to recruit *n* = 120 over 12 months. A minimum sample size of 120 was proposed by Teare et al. for pilot studies with dichotomous outcomes, based on the precision to which binary parameters are estimated for use in the sample size calculation of the full trial [20]. Mortality under standard care is estimated at 12%, and for the full trial, a 5% absolute reduction is postulated (i.e. to 7%) in the intervention arm. With *n* = 120, we will therefore be estimated to within a standard error of 2.7% and used in the sample size calculation for the eventual trial. Given the short follow-up period, loss to follow-up of < 5% at 30 days is envisaged. This sample size will allow estimation of feasibility outcomes with a precision of < 5%.

A previous evidence synthesis study produced estimates of the incidence of eligible cases ranging from 3.5 to 40.8 per 100,000 population per year [3, 9]. The lowest estimates were based upon actual patients treated with CPAP, in services with limited ability to deliver treatment for all eligible patients and are likely to be underestimates. The highest estimates were based upon audit data for in-hospital NIV use among emergency admissions and are likely to be overestimates. Assuming that there are 20 eligible cases per 100,000 population per year and 40% are recruited, 120 patients will be recruited from the study’s source population of 1.5 million, over 1 year.

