**Methods:**

An individual patient randomised controlled external pilot trial will be conducted comparing prehospital CPAP to standard oxygen therapy for ARF. Adults presenting to ambulance service clinicians will be eligible if they have respiratory distress with peripheral oxygen saturation below British Thoracic Society (BTS) target levels, despite titrated supplemental oxygen. Enrolled patients will be allocated (1:1 simple randomisation) to prehospital CPAP (O_two system) or standard oxygen therapy using identical sealed boxes. Feasibility outcomes will include incidence of recruited eligible patients, number of erroneously recruited patients and proportion of cases adhering to allocation schedule and treatment, followed up at 30 days and with complete data collection. Effectiveness outcomes will comprise survival at 30 days (definitive trial primary end point), endotracheal intubation, admission to critical care, length of hospital stay, visual analogue scale (VAS) dyspnoea score, EQ-5D-5L and health care resource use at 30 days. The cost-effectiveness of CPAP, and of conducting a definitive trial, will be evaluated by updating an existing economic model. The trial aims to recruit 120 patients over 12 months from four regional ambulance hubs within the West Midlands Ambulance Service (WMAS). This sample size will allow estimation of feasibility outcomes with a precision of < 5%. Feasibility and effectiveness outcomes will be reported descriptively for the whole trial population, and each trial arm, together with their 95% confidence intervals.

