### Randomisation, allocation concealment and participant enrolment

Patients presenting to ambulance service clinicians with ARF will be individually randomised to CPAP or standard oxygen therapy in a 1:1 ratio using simple, unrestricted randomisation. The randomisation sequence will be computer-generated by an independent statistician who is not directly involved in the conduct of the trial. The allocation sequence will be held centrally on a password-protected, access-restricted network drive. The trial statistician will not have access to the randomisation sequence until after data lock. Due to the physical differences between the CPAP device and standard oxygen mask, it is not possible to blind patients, ambulance service clinicians or hospital clinicians to the treatment arms. Outcome assessors will also not be blinded. However, both primary and secondary endpoints comprise ‘hard’ objective measurements, minimising the possibility of information bias.

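### The unqualified precision of under 5% for feasibility outcomes leaves precision undefined and does not hold for treatment adherence in the CPAP arm, which rests on about 60 patients

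*Protocol article*

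**What the plan says.** The claim closes the sample size paragraph of the protocol article (section *Sample size and statistical analyses*) and also appears in the Methods part of the abstract: "This sample size will allow estimation of feasibility outcomes with a precision of" less than 5%. It is made for the feasibility outcomes as a group, without exception, and precision is not defined.

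The same section lists those outcomes with their targets. They will be reported "together with their 95% confidence interval (calculated using the Wilson score method"). They include "Adherence to the allocation schedule (target ≥ 90"%), retention at 30 days and data completeness, both also with a target of at least 90%, and "Adherence to treatment in the CPAP arm (target ≥ 75"%). The last of these is restricted to one arm by its own wording.

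On size and allocation, "The trial aims to recruit 120 patients over 12 months", and patients are "individually randomised to CPAP or standard oxygen therapy in a 1:1 ratio using simple, unrestricted randomisation". The only precision figure worked out in the section is an SE of 2.7%, given in connection with mortality.

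**The concern.** One figure is given for outcomes with different denominators. Most are measured in all 120 patients, but treatment adherence is measured in roughly half of them and has the lowest target, 75%, where the binomial variance is larger. A bound that suits the whole-trial outcomes need not suit this one.

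This matters because the trial is an external pilot whose primary objectives are feasibility estimates, and the background asks specifically whether CPAP can be delivered within the NHS ambulance service. The discussion section adds that the pilot will estimate adherence precisely enough to support the definitive protocol. A reader who takes under 5% at face value would expect an observed adherence of 75% to be pinned down much more tightly than 60 patients allow.

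**Working it through.** **Inputs, all from the protocol article.** Total n = 120; 1:1 simple randomisation, so about 60 in the CPAP arm; targets of 90% (allocation adherence, retention, data completeness) and 75% (treatment adherence, CPAP arm); 95% Wilson intervals; mortality of 12% under standard care and 7% postulated with CPAP; loss to follow-up under 5%.

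**Formulas.**
- SE = √(p(1−p)/n)
- Wilson half-width = z/(1+z²/n) × √(p(1−p)/n + z²/(4n²)), with z = 1.96
- Wilson centre = (p + z²/(2n))/(1+z²/n)

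**Step 1: the article's own SE.** Pooled mortality is (12% + 7%)/2 = 9.5%, and √(0.095 × 0.905/120) = 2.68%, which rounds to the stated 2.7%. The alternatives do not fit: 12% with n = 120 gives 2.97%, and 12% with n = 60 gives 4.20%. The stated figure is therefore reproduced as a whole-trial SE.

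**Step 2: the 90% targets, n = 120.**
- SE = √(0.90 × 0.10/120) = 2.74%
- Wilson half-width = (1.96/1.0320) × √(0.000750 + 0.0000667) = 5.43 points; interval 83.3% to 94.2%

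**Step 3: the 75% target, n = 60.**
- SE = √(0.75 × 0.25/60) = 5.59%
- Wilson half-width = (1.96/1.0640) × √(0.003125 + 0.000267) = 10.73 points; interval 62.8% to 84.2%

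**Step 4: comparison with the stated bound of 5.**

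| Outcome and proportion | n | SE (%) | Under 5? | 95% Wilson half-width (points) | Under 5? |
|---|---|---|---|---|---|
| Whole trial, 90% | 120 | 2.7 | yes | 5.4 | no, narrowly |
| Whole trial, 92% | 120 | 2.5 | yes | 4.95 | yes |
| Whole trial, 95% (retention as envisaged) | 120 | 2.0 | yes | 4.1 | yes |
| CPAP adherence, 75% | 60 | 5.6 | no | 10.7 | no |

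**Step 5: sensitivity.**
- *Interval method.* Wald half-widths are 5.37 and 10.96 points, so the choice of interval does not matter here.
- *Size of the CPAP arm.* Under simple randomisation its standard deviation is √(120 × 0.25) ≈ 5.5, so it lies roughly between 49 and 71. Even at 71 the SE is √(0.1875/71) = 5.1% and the Wilson half-width is 9.9 points. An SE below 5% at p = 0.75 needs more than 0.1875/0.0025 = 75 CPAP patients.
- *Higher adherence.* With 60 patients the SE falls below 5% from about 82% adherence, and the Wilson half-width falls below 5 points only from about 97%.
- *Any whole-trial proportion.* With n = 120 the SE is at most √(0.25/120) = 4.56%. The Wilson half-width is below 5 points from about 92%.
- *For scale only.* A Wilson half-width under 5 points would take 141 patients at 90% and 286 CPAP patients at 75% (Wald: 139 and 289).

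The recruitment rate per 100,000 is left aside, because its precision is not expressed in percentage points of a proportion.

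**The case against.** The strongest defence is that precision here means SE. The one worked figure in the same paragraph is an SE, and on that reading every whole-trial outcome meets the bound whatever its value. This stands, and it limits the point: on the SE reading only CPAP adherence fails, by a factor of 5.6/5 ≈ 1.1. It does not rescue the sentence, which excepts no outcome.

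Second, the targets are minimums. Retention above 95% is envisaged, and a recruitment-error rate of 0/120 has a Wilson interval of 0 to 3.1%. Both satisfy the claim even as a half-width. This also stands.

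Third, the results will carry 95% intervals, so readers of the final report will see the real uncertainty, and no decision rule in the article uses the 5% figure. That is fair and keeps the consequence modest.

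Three stronger readings may tempt a reader, and the document supports none of them:
- *The claim fails for all feasibility outcomes.* It does not, as the SE and high-proportion rows of the table show.
- *The claim is missed two-fold outright.* The two-fold miss (10.7 against 5) applies to CPAP adherence and only if precision means a 95% half-width.
- *The sample size loses its justification.* The article bases 120 mainly on a cited recommended minimum for pilot studies with dichotomous outcomes and on the SE for mortality. The 5% sentence reads as a consequence of that choice.

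**Conclusion.** The sentence is wrong as written for one listed outcome and ambiguous for the rest. For treatment adherence in the CPAP arm at the 75% target it fails on both available meanings: SE 5.6%, 95% Wilson half-width 10.7 points. An observed 75% would be compatible with anything from about 63% to 84%. For whole-trial outcomes at exactly 90%, the SE of 2.7% meets the bound and the half-width of 5.4 points misses it by 0.4; at about 92% or more both meet it.

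This rests on three assumptions: about 60 patients in the CPAP arm, proportions at their targets, and the CPAP arm as the denominator, as the outcome's wording states. If all 120 patients were counted for the 75% outcome, the SE would be 4.0% but the half-width still 7.7 points. The conclusion for CPAP adherence holds across the plausible range of arm sizes. It concerns a stated figure and does not show that 120 is the wrong size for this pilot.

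**What to change.** Replace the sentence in the abstract and in the sample size section with a defined measure, stated per outcome and denominator. For example:

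> With n = 120 the 95% confidence interval half-width is about 5.4 percentage points for a proportion of 90% (SE 2.7%), and about 10.7 points for 75% treatment adherence in the CPAP arm (n about 60; SE 5.6%).

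If an SE was intended, the sentence should say so and still give CPAP adherence separately. The change is two sentences, and nothing in recruitment, conduct or analysis follows from it. The only downside is that the published figure looks less favourable.
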